**Figure 1 F1:**
[figure not shown]
Flowdiagram. D, Day; EEG, Electroencephalogram; ERG, Electroretinogram; OCT, Optical Coherence Tomography.

#### Between the inclusion visit and the second visit

All participants will wear an actigraph for 21 consecutive days and nights. It measures arm movements in order to assess the quality and quantity of sleep as well as the sleep/wake rhythm. This will be done under the usual living conditions of all participants. They will also complete a sleep diary daily, in the morning after waking up and in the evening before going to bed.

#### Second visit

After the 21 days of recording in actigraphy, a second visit will be offered between day 22 and day 27. First, the actigraph will be removed and a new self-administered questionnaire assessment of sleep and circadian rhythms will be performed. All participants should also bring back the completed sleep diary. Secondly, mood will again be assessed using MADRS and YMRS in order to ensure that all participants are euthymic and neuropsychological evaluations will be carried out with a trained neuropsychologist to assess cognitive function (21, 22). These evaluations will last approximately 2:30 h. The duration of the second visit will be ½ day for all participants. At the end of the second visit, participation in this study (main study) will be over.

#### Optional ancillary study

Patients with BD participating in the study will be offered to participate in an optional ancillary study. They will be informed during the initial visit about the optional ancillary study by the investigator. If they agree to participate, the investigator will obtain informed and written consent on a specific form for this ancillary study. The aim of the ancillary study will be to assess the impact of BD on the retinal structure and microvasculature using Spectral Domain Optical Coherence Tomography (SD-OCT) and OCT-Angiography (OCT-A). SD-OCT and OCT-A are non-invasive imaging techiques that allow to obtain, in a few minutes, cross-sectional images of the retina and an analysis of its vascularity. This will allow us to measure in particular the central macular thickness, the foveal avascular zone area in the superficial capillary plexus, as well as the vessel density of global superficial capillary plexus, deep capillary plexus and choriocapillaris plexus. These examinations will be carried out between day 23 and day 28 (after the second visit) at the Regional University Hospital of Nancy in the ophthalmology department by an experienced ophthalmologist and will last about 10 min.

### Devices

#### Retinaute^®^ (BioSerenity)

The Retinaute^®^ is a portable medical device developed by BioSerenity, France, for performing an ERG. It comes in the form of a virtual reality headset, which can be used in outpatient facilities. It is non-invasive and uses skin electrodes for the collection of parameters. Electrodes will be positioned on the lower eyelid, on the temple and on the forehead, 1 cm above the eyebrows, according to the recommendations of the developer (BioSerenity). fERG allows to study the retina in a global way thanks to a light flash delivered over the entire surface of the retina. The two main analysis parameters are the a-wave and the b-wave with two main components: the amplitude measured in microvolts and the implicit time measured in milliseconds. This allows the study of photoreceptors with the a-wave and bipolar cells with the b-wave. The Retinaute^®^ also allows the realization of a PERG to precisely study the macular area of the retina. The two main parameters are the P50 and N95 waves with two main components: the amplitude measured in microvolts and the implicit time measured in milliseconds. The P50 wave allows the study of the retinal first two layers (photoreceptors and bipolar cells). The N95 wave specifically studies ganglion cells.

PERG and fERG are performed according to the standards of the International Society for Clinical Electrophysiology of Vision (ISCEV) (23, 24). For the PERG measurements, the stimulus is a black and white contrast reversible checkerboard, with 0.8° check size, 93.3% contrast level, 100 cd/m^2^ constant luminance white area, and 4 reversals per second. Dark-adapted 0.01 fERG, dark-adapted 3.0 fERG and dark-adapted oscillatory potentials, are performed after 20 min of dark adaptation. The stimulus in each case was a flash with a strength of 0.01 and 3.0 candela^*^s/m^2^, respectively. Oscillatory potentials are recorded to the 3 candela^*^s/m^2^ flash stimuli. Then, after 10 min of light adaptation with a light background set at 30 cd/m^2^, light-adapted 3.0 fERG and light-adapted 3.0 flicker fERG are recorded. The stimulus is a flash with a strength of 3.0 candela^*^s/m^2^. These signals will be supplemented with 4 EEG channels, *via* cup electrodes applied to the skull and allowing the concomitant performance of an EEG.

Patients will keep their ocular correction for the pattern protocol. They will then remove their correction for the flash protocols. Visual acuity well be measured before the ERG using the Monoyer scale. Averaged retinal responses will first be obtained for each eye, then the parameters (implicit time and amplitude) will be averaged over both eyes for analysis. It is this average result that will be used for the statistical analyses. The examination is painless, non-invasive and takes ~1 h.

#### Actigraphy

Actigraphy is an ecological and non-invasive method allowing a reliable characterization of the sleep/wake cycle. It is a portable system for continuously measuring the motor activity of an individual and appreciating the alternation of activity periods (wakefulness) and rest periods (sleep). An actigraph (MotionWatch8^®^, CamNtech) looks like a wristwatch that will be worn continuously, by convention on the wrist of the non-dominant hand, over periods ranging from several days to several weeks (here 21 days). The actigraph has a button that subjects are invited to press at bedtime and when they wake up, indicating visual markers that will be used during signal analysis (MotionWare^®^ software, CamNtech). This technique is considered the most relevant of the objective, non-invasive measures of sleep disturbances and circadian rhythms currently available and is recommended by the American Academy of Sleep Medicine (AASM) in the study of the sleep/wake cycle. All participants will be able to continue all the usual activities except sea bathing. Actigraphy does not present a known risk.

#### Optical coherence tomography

The SD-OCT is a modern ocular imaging process using infrared radiation and allowing to obtain in a few seconds, and in a non-invasive way, images in section of the eye. It thus generates images of the retina, the optic nerve, the cornea, the anterior chamber, and the iridocorneal angle. The OCT-A module increments on the OCT. It can detect the movement of the blood elements from sequential SD-OCT slices taken at the same location of the retina and obtain a map of the retinal and choroidal vessels, without injection of fluorescent dye. The device used for both exams will be the OCT spectral RS 3,000 Advance 2 + Angioscan (NIDEK, Gamagori, Japan). The images obtained are displayed on a screen and then analyzed using the built-in NIDEK software. SD-OCT and OCT-A examinations are fast, painless, non-contact and last less than a minute. There is no particular risk.

### Measures and outcomes

#### Primary outcomes: ERG measurements

An electrophysiological measurement with fERG and PERG will be carried out to all participants using the Retinaute^®^ device (BioSerenity). The fERG allows the retina to be studied globally. The main analysis parameters recorded will be the amplitude (microvolts) and implicit time (milliseconds) of the a-wave (cones and rods) and the b-wave (bipolar cells). The PERG is used to study the macular area of the retina. Main parameters recorded will be the amplitude (microvolts) and the implicit time (milliseconds) of the P50 (photoreceptors and bipolar cells) and N95 (ganglion cells) waves.

#### Secondary outcomes

##### EEG measurements

With using 4 EEG electrodes connected to the Retinaute^®^ (BioSerenity), we will measure the latency and amplitude of the P100, N170 and N200 waves.

##### Sleep and activity settings

###### Self-assessment questionnaires

Subjective quality of sleep will be assessed by the Pittsburgh Sleep Quality Index (PSQI) (25) which is a 19-item self-assessment questionnaire that investigates the subjective sleep quality during the past month. The daytime sleepiness and severity of insomnia will be evaluated using respectively the Epworth sleepiness scale (ESS) and the Insomnia Severity Index (ISI) (26, 27).

All participants will also complete circadian self-administered questionnaires such as the Horne and Ostberg circadian typology questionnaire, the Composite Scale of Morningness (CSM) and Circadian Type Inventory (CTI) which characterize the phase, amplitude and stability of sleep/wake rhythms (28–30). Finally, the Berlin Questionnaire will be used to estimate the risk of Obstructive Sleep Apnea syndrome (OSA) (31).

###### Actigraphy and sleep diary

All participants will continuously wear on the wrist of their non-dominant hand for 21 consecutive days and nights an actigraph to characterize the sleep/wake cycles and estimate the quantity and quality of sleep. The main sleep parameters measured will be: sleep duration, sleep latency, Wake After Sleep Onset (WASO), sleep efficiency, Fragmentation Index (FI). The main activity parameters recorded will be: Inter-daily Stability (IS), Intra-daily Variability (IV), the relative amplitude of activity and the L5 onset and the M10 onset which corresponds to the onset time of the 5 hours least active and the 10 most active hours during the 24-h cycle. Concomitantly with actigraphy, all participants will complete a sleep diary during these 21 days on which they will register the time they turned off the light to go to sleep, their subjective estimates of sleep latency and the time they got up the next morning.

##### Neuropsychological assessments

The purpose of this assessment is to establish a cognitive profile for each participant. It uses a series of tests widely described in the literature and commonly used today. Several tests would evaluate cognitive functions, including an assessment of verbal episodic memory (California Verbal Learning Test), usually impaired in BD (32). Other cognitive functions such as executive functions would be evaluated thanks to the Test of Attentional Performance (TAP) through the working memory, flexibility and incompatibility subtests (33). In order to complete the executive assessment, the verbal fluency test would be provided (34). Sustained attention is frequently impaired in euthymic BD and will be investigated with the Conners' Continuous Performance Test 3rd Edition (CPT-III) (35). Since aging subjects could be included in the study, the Montreal Cognitive Assessment (MoCA) will be dispensed to detect the presence of mild cognitive impairment (36). Finally, a visual perception test using the Visual Object and Spatial Perception (VOSP) will be performed to inspect visual cognition (37).

##### Clinical assessments

The aim of the clinical evaluation is to characterize the disease in the group of patients. We will therefore look for: family psychiatric history, lifetime comorbidities, number and characteristics of manic, hypomanic and depressive episodes, the age of the first mood episode, the polarity of the first episode and the dominant polarity, the presence of a history suicide attempt, the presence of rapid cycling, mood episodes induced by treatments. We will also characterize the type of BD and research prescribed psychotropic treatments and assess their tolerance and drug response.

#### Other outcomes

As part of the usual management of patients with BD at the Expert Center for BD in Nancy, self-questionnaires evaluating “trait” and “state” markers of the disease will be submitted to patients. Data collected in these questionnaires will perhaps make it possible to identify relations with electrophysiological markers. The “state” questionnaires include an assessment of mood with the Quick Inventory of Depressive Symptomatology self-report (QIDS-SR) and the Altman Self-Rating Mania Scale (ALTMAN), anxiety will be assessed by the State Trait Inventory Anxiety (STAI-A), emotional reactivity will be assessed by the Multidimensional Assessment of Thymic States (MATHYS) and tolerance and adherence to treatments will be assessed by the Patient Rated Inventory of Side Effects (PRISE-M) and the Medication Adherence Rating (MARS) (38–43). Patients treated with lithium will complete the Alda Scale to assess response to treatment (44). The patient's functioning will be assessed using the Functioning Assessment Short Test (FAST) and the Clinical Global Impression Scale (CGI), allowing an assessment of symptom severity and response to treatment (45, 46).

The “trait” questionnaires include an assessment of intensity and emotional lability assessed by the Affective Instability Measure (AIM) and the Affective Lability Scale (ALS), impulsivity and hostility by the Buss-Durkee Hostility Inventory (BDHI) and the Barrat Impulsivity Scale (BIS-10), the search for an antecedent of Attention Deficit/Hyperactivity Disorder will be done using the Wender Utah Rating Scale (WURS) and finally, the search for trauma in childhood will be carried out with the Childhood Trauma Questionnaire (CTQ) (47–52).

Finally, all participants will complete the Fagerström Test to evaluate tobacco dependence and the Edinburgh Handedness Inventory (EHI), which assesses manual preference for determining the wearing side of the actigraph (53, 54).

#### Ancillary study outcomes

This evaluation will only be offered to patients with BD who have given their consent for the ancillary study during a specific visit organized between day 23 and day 28 (after visit n ° 2). SD-OCT will measure central retinal thickness as well as nerve fiber and ganglion cell layer thickness. OCT-A will measure the size of the central avascular zone as well as measure the fractal dimension and vascular density and skeletal density of the global superficial capillary plexus, deep capillary plexus and choriocapillaris plexus.

All measurements performed during this study are summarized in Figure 2.

**Figure 2 F2:**
[figure not shown]
Schedule of enrolment, interventions and assessments. *, Only concerns patients; BD, Bipolar Disorder; CPT, Conners' Continuous Performance Test; CVLT, California Verbal Learning Test; D, Day; EEG, Electroencephalogram; EHI, Edinburgh Handedness Inventory; ERG, Electroretinogram; fERG, electroretinogram flash; MADRS, Montgomery and Asberg Depression Rating Scale; MINI, Mini International Neuropsychiatric Interview; MoCA, Montreal Cognitive Assessment; OCT, Optical Coherence Tomography; PERG, electroretinogram pattern; TAP, Test of Attentional Performance; VOSP, Visual Object and Spatial Perception; YMRS, Young Mania Rating Scale.

### Sample size

Since 2010, analysis of the literature, by synthesizing the results of comparable studies, shows that the ratio between the variability and the clinical difference between healthy subjects and subjects with similar pathologies is generally around 0.5 (for delta/standard deviation or around 2 for standard deviation/delta). With an alpha risk of 5% and a statistical power of 80%, such an effect size leads to a number of 64 subjects per group. With 10% lost to follow-up and/or non-exploitable data, the number of subjects to be recruited in each group is 70. From these elements we therefore set the number of participants to be recruited at 140 subjects: 70 subjects in the patient group and 70 subjects in the healthy control group.

### Statistical analysis

Both descriptive and comparative analyses will be conducted by accounting for the nature and distribution of the variables. Qualitative variables will be described with frequencies and percentage; quantitative variables with the mean ± SD (standard deviation) or with the median (Inter Quartile Range). For quantitative variables, the Student's *t*-test or the Mann-Whitney U test will be used and for qualitative variables, the chi-square test with, if necessary, the exact calculation of Fisher. The Pearson's coefficient or the Spearman's rho will allow analysis of the correlations. A multivariate analysis will be conducted according to the results of univariate analysis. Regarding the analysis of ERG parameters, after checking the distribution, these will be analyzed *via* generalized estimating equations (GEE) in case of gamma distribution. This is a robust statistical method relevant in the analysis of repeated measures with non-normal response variables (55). Finally, a receiver operating characteristic curve (RoC) will be generated for variables that differed between groups in order to dichotomize the variables of interest and calculate the associated sensitivity and specificity values.

An intermediate data analysis is planned 9 months (mid-term study) after the start of inclusions. The statistical significance level is set at 1% for the interim analysis and 4% for the final analysis. IBM™ SPSS Statistics v23 will be used for the data analysis.

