## Methods

### Study design

The BiMAR study is an exploratory, open-label and non-randomized comparative moncentric study applied in psychiatry and neuroscience. This research included two groups of adult subjects: a group of patients with BD in the euthymic phase and a group of healthy control subjects. No blinding procedure is planned in this research.

The BiMAR study protocol was reviewed and approved by the French ethics committee (Comité de Protection des Personnes, Ile de France IV) under the reference 2021/60. The study is also registered at Clinicaltrials.gov under the number NCT05161546. All participants in this research will give their written informed consent before the start of any clinical interview, assessment or measurement.

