### Setting and participants

This study will include two groups of participants. A group of euthymic patients with BD and a group of healthy control subjects. Patients eligible for the study will be recruited from the outpatient population followed at the Expert Center for BD in Nancy (France) or followed on an outpatient basis in consultation services of the Psychotherapeutic Center of Nancy. Healthy subjects eligible for the study will be recruited locally from the general population, after a call for volunteers using posters and flyers. A first telephone contact, at least 15 days before the first visit, with interested participants will allow them to present the study in more detail, to verify the main eligibility criteria and to set an appointment for the inclusion visit.

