### Inclusion and exclusion criteria

Inclusion criteria for patients were as follows: (1) been diagnosed with BD according to DSM-IV diagnostic criteria using the Mini International Neuropsychiatric Interview (MINI) (20); (2) been currently euthymic for at least 3 months prior to the study, as defined by a score below 10 on the Montgomery-Asberg Depression Rating Scale (MADRS) which assesses depression (21) and by a score below 8 on the Young Mania Rating Scale (YMRS) which assesses mania (22); (3) age 18 or more. Healthy volunteers must not suffer from a personal psychiatric pathology verified with the MINI and be at least 18 years old (20).

Non-inclusion criteria for all participants (patients and healthy subjects) are suffering from psychiatric pathology or substance use disorders according to DSM-IV criteria measured with the MINI (20), excluding BD for the patient group; suffering from neurological or retinal pathology; having a shift work or a jet-lag in the last 15 days; criteria incompatible with the use of the virtual reality headset (Retinaute^®^, BioSerenity) like having an allergy to one of the components of the textile. We will also not include persons treated by sismotherapy during the past year, persons with an uncorrected visual impairment or disabling hearing impairment that does not allow neuropsychological tests to be performed. Finally, pregnant or breastfeeding women will also be excluded as well as subjects with an intellectual disability making it difficult to participate in the study or to understand and follow informations provided to them, adults legally protected, subjects already participating in another interventional trial.

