Certain limitations inherent in the interventions are known and described. They will be considered in this study. Indeed, several conditions may be associated with changes in the function and/or retinal structures. We can cite certain medical comorbidities such as obesity, diabetes, OSA, the consumption of certain toxic substances including tobacco, as well as the taking of certain medications (15). However, these comorbidities are frequently associated with BD and the disease requires long-term treatment. We know that these factors can have an impact on the ERG signal or even EEG. This is the reason why we will take it into account when processing and analyzing the data. Recording in actigraphy requires all participants to remember to press the button on the watch when going and getting out of bed. It may nevertheless be compensated through the sleep diary that will correct missing data. Also note that participants with time awake during the night by staying completely still could be counted as sleep by the device and thus overestimate sleep duration. We know that performing neuropsychological tests can require a significant attentional load, especially for patients who may have residual cognitive impairment associated with BD. This will be offset by the organization of breaks during the execution of the tests.

The ancillary study will consist of carrying out an OCT examination for the group of patients. This complementary module will allow the study of retinal structural changes within a significant sample with regard to data from the literature (56). We will also carry out a study of the retinal microvasculature, for which there is no data in the literature, to our knowledge, in patients with BD.

Finally, one of the specificities and strengths of the BiMAR study is to concomitantly combine the study of several electrophysiological markers and to associate a search for a relationship with circadian, sleep and neuropsychological markers.

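### The ERG group comparison names no covariates and lets univariate results decide adjustment, although the article concedes known ERG confounders; treatment is also nearly aliased with group

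*Protocol article*

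**What the plan says.** The Study design section calls this an "exploratory, open-label and non-randomized comparative moncentric study applied in psychiatry and neuroscience". Patients are outpatients of the expert centre or of the consultation services of the same institution. Controls are "recruited locally from the general population, after a call for volunteers using posters and flyers". Both groups must be at least 18, with no upper age limit, and the Neuropsychological assessments section expects older participants ("Since aging subjects could be included in the study"). No matching or quota is stated.

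The Statistical analysis section names the t-test or Mann-Whitney test for quantitative variables, and GEE for ERG parameters if they follow a gamma distribution. It names no covariate. On adjustment it says only: "A multivariate analysis will be conducted according to the results of univariate analysis". ROC curves are then drawn for variables that differ between the groups.

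The Discussion lists obesity, diabetes, sleep apnoea, toxic substances including tobacco, and some medications as factors that can change retinal function. It says they are common in bipolar disorder and that "the disease requires long-term treatment", and it concludes: "This is the reason why we will take it into account when processing and analyzing the data". No method is given. Age and sex are not in that list, although the Inclusion visit section collects both. On controls, the criteria say: "Healthy volunteers must not suffer from a personal psychiatric pathology verified with the MINI".

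**The concern.** In a non-randomised comparison, covariates should be chosen because they are known or expected to affect the outcome, not because of a p-value in the sample. The article states the opposite rule, and that rule fits poorly with its own promise to account for known ERG confounders. Two consequences follow.

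- If the reported result is the unadjusted contrast, an imbalance in age, sex or a comorbidity can create a difference or hide a real one. That difference may then go on to the ROC step and be presented as a candidate marker.
- Treatment will sit almost wholly in the patient group. Adding a medication term to the between-group model is the obvious way to keep the Discussion's promise, but it will have little power to separate disease from drug.

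**Working it through.** **The plan's own figure.** For an effect of 0.5 SD, two-sided 5% alpha and 80% power, the t-test needs 63.8 per group, hence the stated 64. The calculation assumes an unadjusted two-group difference. Below I use 63 per group (70 less 10%) and the final alpha of 4%. Power for d = 0.5 is then 76.7%.

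**Age imbalance.** The documents give no age distribution and no age–ERG correlation. Assumptions: age SD 14 years, within-group correlation r of 0.3–0.5, no true group effect.

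- Bias in SD units: b = (age gap / 14) × r.
- Noncentrality: b × √(63/2), on 124 degrees of freedom, two-sided 4%.
- Example, 7 years and r = 0.3: b = 0.5 × 0.3 = 0.15; noncentrality = 0.15 × 5.61 = 0.84; rejection rate 11.3%.

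| Age gap | r = 0.3 | r = 0.5 |
|---|---|---|
| 2.5 years | 4.9% | 6.5% |
| 3.5 years | 5.8% | 9.0% |
| 7 years | 11.3% | 25.4% |
| 10 years | 19.5% | 47.4% |

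In simulation, a model with age always included keeps about 4%.

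If a 7-year gap runs against a true d of 0.5, the unadjusted effect is 0.5 − 0.15 = 0.35 or 0.5 − 0.25 = 0.25. Power falls from 76.7% to 45.8% or 25.4%. With age in the model it is about 78% or 85%.

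**Screening as such.** Simulations with one confounder, 64 per group, imbalances of 0.25–0.75 SD and r of 0.3–0.5 compared a fixed covariate with one entered only if significant univariately. False-positive rates were 3.9–4.2% (fixed) and 3.9–4.5% (screened). Screening a single covariate is therefore close to nominal. The numerical risk lies in relying on the unadjusted contrast.

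**Medication.** The treated shares are not given. Assumption: 90–95% of patients and 0–2% of controls take a psychotropic. With equal groups, treated shares p and q, and m = (p + q)/2:

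- φ² = [(p − q)/2]² / [m(1 − m)]; variance inflation = 1/(1 − φ²).

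| Patients / controls treated | φ | Variance inflation | SE ratio | Power, d = 0.5 |
|---|---|---|---|---|
| 90% / 2% | 0.88 | 4.5 | 2.1 | 23% |
| 90% / 0% | 0.90 | 5.5 | 2.3 | 19% |
| 95% / 2% | 0.93 | 7.4 | 2.7 | 15% |
| 95% / 0% | 0.95 | 10.5 | 3.2 | 12% |

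At 100% versus 0% the group effect adjusted for medication cannot be estimated. With 70% or 80% of patients and no controls treated, variance inflation is 2.2 or 3.0 and power (64 per group) about 45% or 34%.

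**The case against.** The strongest reply is that a journal article condenses a fuller plan, so a covariate list, or even matching, may exist elsewhere. That stands as far as it goes. A reader might infer that the groups are unmatched and that the ERG models contain no covariates, but the article is silent on matching and simply names no covariate for the GEE. What it does state is the rule that adjustment follows univariate results.

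Three other inferences go too far.

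- **ROC input.** A reader might take it that ROC variables are chosen by unadjusted tests. The article says only that they differed between groups, after describing both the univariate and the multivariate step. The input is open, not fixed wrongly.
- **Inseparable treatment.** That medication cannot be separated from group is true only if all patients and no controls are treated, which is not stated. Treatment is recorded, and relating patients' clinical phenotype to the ERG is already a secondary aim, so within-patient analyses fit the plan.
- **Age and sex as documented confounders.** The article does not list them as affecting the ERG. The remark on older participants explains why a cognitive screen is given. The age figures rest wholly on assumptions, and small gaps do little harm.

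It is also fair to say that confounding by treatment is inherent in comparing treated patients with healthy controls, and that the authors acknowledge it. What remains is that the acknowledgement has no method behind it and conflicts with the stated selection rule.

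**Conclusion.** The point holds and should be fixed. The stated adjustment rule is data-driven, does not match the Discussion's promise, and leaves age and sex unnamed in a non-randomised comparison. Under the assumptions shown, the harm to the unadjusted test runs from negligible (about 5% false positives) to serious (about 47%), depending on the imbalance that recruitment happens to produce. For medication, an adjusted between-group estimate would be too imprecise to settle the question if nearly all patients are treated.

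A reader might rate this as a fault that invalidates the study. The documents do not support that: the study is labelled exploratory, its output is candidate markers for confirmation in larger samples, a multivariate step is foreseen, and the needed variables are collected.

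**What to change.** - Make the primary ERG analysis a regression or GEE of each parameter on group, with age and sex always included. Delete selection by univariate results.
- Add one fixed sensitivity model with BMI, tobacco, Berlin sleep-apnoea risk and diabetes. Height, weight, medical history, the Fagerström test and the Berlin questionnaire are collected in all participants.
- Choose the variables for the ROC step from the adjusted model, and say so.
- Do not rely on a medication term in the between-group model. Describe ERG parameters by drug class within patients, as exploratory. State that the contrast is treated euthymic bipolar disorder versus controls and cannot by itself separate disease from treatment. Comparing patients not taking a given class with controls would not solve this, since they may take other classes.
- Optionally, fill remaining control places to mirror the patients' age and sex. This depends on places remaining, as recruitment was due to end in July 2023.

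The cost is wording and a few models on data already collected. No change in sample size is needed on this account. Control quotas, if used, might slow recruitment slightly.
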